### Training, supervision and fidelity checks

The study RA has received training to deliver screening interviews and collect data. The trial EMDR-trained psychological therapists have attended training on the FND-specific EMDR protocol, delivered by the chief investigator (SC). They receive regular clinical supervision from SC, as well as external supervision from an EMDR consultant (a requirement of offering EMDR). Therapists will complete a session record form after every session, and these will be reviewed in supervision to enhance fidelity.

All sessions of EMDR will be video-recorded and the recordings stored on the secure SWLSTG NHS server. The therapists will share access to the recordings with SC for supervision purposes, and excerpts will be shown in EMDR supervision. Randomly selected recordings of processing sessions will be rated for fidelity, using the EMDR Fidelity Rating Scale Version 2—Adverse Life Experiences Processing subscale, by an EMDR Consultant.^35^ These scores will be analysed to evaluate fidelity.

### Primary objectives and outcome measures

A mixed-methods approach will be used to establish feasibility and acceptability. The feasibility criteria and progression criteria are summarised in table 3.

**Table 3 T3:** Feasibility criteria and progression criteria for MODIFI

Criterion	Critical feasibility outcome	Other feasibility and acceptability data relevant to the criterion	Proposed threshold on critical outcome
Recruitment rate	Percentage potentially eligible participants attending screening interview	Number of potentially eligible participants identified during neuropsychiatric assessment Number of participants who consent and are randomised Reasons for non-eligibility	Above 70% attending a screening interview of those approached to participate, and if attendance is less than 70%, ways to increase the screening interview attendance rate will be considered.* If 50%–70% attend a screening interview of those approached to participate, and if attendance is less than 70%, ways to increase the screening interview attendance rate will be considered.† If below 50% attend screening interview of those approached to participate, feasibility will not be demonstrated.‡
Intervention adherence	Percentage of participants randomised to EMDR+NPC who complete therapy (completion=attendance of 8 or more sessions, maximum session number=16)	Qualitative interviews with participants who attend EMDR Therapy session record forms Average number of sessions attended per course of therapy	Feasibility will be demonstrated if above 70% complete therapy (attend eight or more EMDR sessions).* If 50%–70% participants complete therapy, ways to improve engagement will be considered.† If <50% participants complete therapy, feasibility will not be demonstrated.‡
Outcome measurements completion	Percentage of participants who complete outcome measures at all time points	Retention of participants (rates of withdrawal across both arms) Reasons for withdrawal Qualitative interviews with participants	Feasibility will be demonstrated if above 70% of participants complete outcome measures at each time point.* If 50%–70% of participants complete outcome measures at all time points, ways to improve retention and completion of outcome measures will be considered.† If <50% of participants complete outcome measures at all time points, feasibility will not be demonstrated.‡

*Continue to main study without modifications.

†Future definitive trial is feasible with modifications.

‡Future definitive trial is not feasible.

EMDR, eye-movement desensitisation and reprocessing therapy; NPC, neuropsychiatric care.

Assessment of safety (adverse/serious adverse events) will be compared between the two arms. Therapy satisfaction and therapy fidelity will also be examined. The outcome measures used will be evaluated and the primary outcome measure identified, and the required sample size for a substantive RCT will be calculated.

The nested qualitative study will explore participants’ and treating therapists’ experiences and views. Information from these interviews will inform design and trial materials for a substantive study, including the FND-specific EMDR protocol. As the feasibility trial includes the option of attendance of appointments virtually, take up of this option will be measured.

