### Study design

This feasibility study is a single-blind RCT with two arms: EMDR (plus standard neuropsychiatric care (NPC)) and standard NPC only. The two groups will be compared at baseline (T0), 3 months (T1), 6 months (T2) and 9 months (T3). Fifty adult patients with a diagnosis of FND, confirmed by a neurologist according to standardised diagnostic criteria, will be recruited via a UK neuropsychiatry service. The research assistant (RA) and project statistician will be blind to treatment allocation. After the intervention period, semistructured interviews will be carried with a proportion of participants and clinicians to explore their experiences and views about the trial.

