### Analysis and statistical methods

#### Sample size

This is a feasibility trial; as such, a power calculation is neither possible nor necessary. Rather, the sample size is pragmatic. Target recruitment is 50 patients in total (25 in each arm), which is consistent with those recommended for pilot and feasibility studies to provide sufficiently reliable estimates of feasibility outcomes, for example, recruitment, adherence and attrition rates and adequate precision of means and variances to inform a fully powered RCT.^39–41^

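### Table 3, outcome completion: the green band is worded per visit while amber and red use completion at all time points, so the bands can overlap

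*Protocol article*

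**What the plan says.** The row is in Table 3 of the protocol article, section 'Primary objectives and outcome measures'. It has four relevant parts:

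- Critical outcome: "Percentage of participants who complete outcome measures at all time points".
- Green: "Feasibility will be demonstrated if above 70% of participants complete outcome measures at each time point". The footnote gives the consequence: "Continue to main study without modifications".
- Amber: "If 50%–70% of participants complete outcome measures at all time points", in which case ways to improve retention and completion are to be considered.
- Red: "If <50% of participants complete outcome measures at all time points, feasibility will not be demonstrated". The footnote gives the consequence: "Future definitive trial is not feasible".

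The threshold column is headed as applying to the critical outcome. The other two rows of the table each keep one percentage through all three bands. The section 'Statistical analysis plan' uses the green band's phrase for something else: retention estimated visit by visit, separately for each measure. It also says that feasibility outcomes will be compared with the progression criteria.

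**The concern.** Completion at all time points is counted within a person: a participant counts only if no visit is missing. Completion at each time point, read literally, is a separate rate for every visit, and different people may be missing at different visits. The second quantity can never be lower than the first. A green band set on the more lenient quantity, beside amber and red bands set on the stricter one, does not divide the possible results into three exclusive classes.

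This is one of only three progression criteria in a trial whose purpose is to judge whether a larger trial is feasible. If two bands apply to the same data, the printed rule does not say which one governs. In the likelier case, what is at stake is whether the main trial proceeds unchanged or with measures to improve retention.

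**Working it through.** The article gives no figure to reproduce for this criterion, so the check is a direct count.

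**Inputs.** N = 50, from 'Sample size'. Four time points, T0 to T3, from 'Study design'. Cut-offs of 70% and 50%, from Table 3. Assumption: T0 is complete for everyone randomised, because the trauma questionnaire is needed for stratification. That leaves T1, T2 and T3 able to go missing.

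**Smallest green count.** 35/50 is exactly 70%, which is not above 70%. The literal green rule therefore needs at least 36/50 (72%) at every visit.

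**Completion at all time points when k of 50 complete each of T1 to T3.**

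- Lowest possible, when different people are missing at each visit: max(0, 50 − 3 × (50 − k)).
- Highest possible, when the same people are missing (nested, as in monotone dropout with equal rates): k.
- Expected share if missingness is independent between visits: (k/50)³.

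| k per visit | Lowest | Independent | Highest |
|---|---|---|---|
| 36 (72%) | 50 − 42 = 8 (16%) | 37% | 36 (72%) |
| 40 (80%) | 50 − 30 = 20 (40%) | 51% | 40 (80%) |
| 41 (82%) | 50 − 27 = 23 (46%) | 55% | 41 (82%) |
| 42 (84%) | 50 − 24 = 26 (52%) | 59% | 42 (84%) |
| 45 (90%) | 50 − 15 = 35 (70%) | 73% | 45 (90%) |
| 46 (92%) | 50 − 12 = 38 (76%) | 78% | 46 (92%) |

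Every row meets the literal green rule. Red (below 25) is also reachable up to k = 41. Amber (25 to 35) is also reachable up to k = 45. From k = 46 only green is possible.

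**Independence limits.** The expected share complete throughout is below 50% when the per-visit rate is below 0.5^(1/3) = 79.4%. It is at or below 70% when the per-visit rate is at or below 0.7^(1/3) = 88.8%.

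**A worked overlap.** Let 40/50 complete each of T1, T2 and T3, with a different 10 people missing each time. Every visit is at 80%, so green is met. Only 20/50 (40%) are complete throughout, so red is met too.

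**No gap.** If any visit is at or below 70%, completion at all time points is also at or below 70%, so amber or red applies. The fault is overlap only.

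**How likely.** A simulation of 10,000 trials took a true 80% completion at each of T1 to T3 and a shared normal latent factor to make missingness correlate within a person. The correlations and the 80% are assumptions, not figures from the article.

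| Latent correlation | Green and amber | Green and red |
|---|---|---|
| 0 | 59% | 24% |
| 0.3 | 76% | 5% |
| 0.6 | 72% | about 0% |
| 0.9 | 30% | 0% |

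**If T0 could also be missing.** The lowest count becomes 50 − 4 × (50 − k), floored at zero. Green with red is then possible up to 43/50 (86%), and green with amber up to 46/50 (92%).

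**The case against.** The strongest reply is that the table already settles the matter. Its column header ties the thresholds to the critical outcome, that outcome is completion at all time points, and the three cut-offs form one continuous scale. On that view the word *each* in the green band is loose wording for *every*, meant within a person, and the conflict disappears. This stands as a good guide to what was probably intended, and it decides the direction of the fix. It does not remove the inconsistency. The wording changes within one cell, nothing says the two phrases are equivalent, and the analysis section uses the green phrase for per-visit rates.

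A second reply is that loss may be mostly monotone. The row lists withdrawal as companion data, and 'Standard NPC' describes participants who start excluded treatment and cannot complete the trial. Under purely monotone loss, completion throughout equals the lowest per-visit rate and nothing conflicts. This stands as a limit on size. Intermittent gaps remain plausible, because several questionnaires and a two-week daily app diary fall at every time point.

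A reader might also infer that the verdict will be picked once the completion data are known. The article does not support that. Analysis is to follow a statistical analysis plan agreed with the trial steering committee beforehand. That plan is not shown, so it may or may not resolve the wording.

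**Conclusion.** Wrong as written, in a limited form. Read literally, the green band uses a more lenient quantity than the row's stated critical outcome, and it overlaps amber and, in a narrower range, red. With N = 50, complete T0 data and equal rates at T1 to T3, overlap with amber is possible from 72% to 90% per visit, and overlap with red from 72% to 82%.

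A reader might infer that the rule typically returns both *continue* and *not feasible*. The figures do not support that. Green with red needs many participants missing different visits. At a true 80% per visit its simulated probability falls from about 24% under independence to about 5% at a latent correlation of 0.3, and to practically nothing at 0.6. Green with amber is the conflict to expect, and it persists under strong within-person correlation (30% at 0.9). It vanishes only if dropout is purely monotone or the two phrases are taken to mean the same.

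**What to change.** In the green band of this row, replace *each time point* with *all time points*, so that all three thresholds apply to the stated critical outcome. At N = 50 the bands become green 36 or more, amber 25 to 35 and red 24 or fewer, which are mutually exclusive and exhaustive. The worked overlap above (20/50 complete throughout) then has one verdict, red. Agree the change with the trial steering committee before completion data are reviewed. Report per-visit completion as supporting data, as the analysis section already plans.

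There is no need to confine the criterion to a candidate primary questionnaire or to set the app diary aside. The primary measure is still to be identified from this trial, and the diary is the article's measure of functional symptoms.

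The cost is a small wording change. Green becomes somewhat harder to reach than under the per-visit reading. If all time points was always meant, nothing changes in substance.

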### Outcome measures

In terms of assessing FND, there is no single validated outcome measure for FND symptoms available.^36^ Ecological Momentary Assessment (EMA) using the m-Path App will be used to assess FND symptoms. Participants will rate a maximum of two symptoms, chosen at the beginning of the trial period, for example, seizures, tremor, limb weakness, tingling/numbness, gait disturbance, for a 2-week period at each time point. For each of the two symptoms chosen, they will answer five questions daily (frequency, severity, interference, associated distress, associated preoccupation), and the mean for each item will be calculated for each 2-week period at each time point.

The schedule of enrolment, interventions and assessments for participants is illustrated in table 4. For descriptions of outcome measures, please see online supplemental material.

10.1136/bmjopen-2023-073727.supp1Supplementary data

**Table 4 T4:** Schedule of enrolment, interventions and assessments for participants

	Screening	Baseline (T0)	3 Months (T1)	6 Months (T2)	9 Months (T3)	Post-trial period
Enrolment						
Consent to contact obtained by clinical staff (neuropsychistrist)	x					
Contacted by RA to arrange screening interview	x					
International Trauma Exposure Measure (ITEM)^37^	x					
Multiscale Dissociation Inventory (MDI)^38^	x		x	x	x	
Informed consent	x					
Demographics recorded	x				x*	
History of psychological therapy		x				
Current medication		x				
Randomisation allocation		x				
Interventions						
EMDR						
NPC						
Assessments						
WHO Disability Assessment Schedule (WHODAS 2.0)^46^		x	x	x	x	
EQ-5F-5L^47^		x	x	x	x	
Ecological momentary assessment of FND symptoms via m-Path App		x	x	x	x	
PHQ-9^48^		x	x	x	x	
GAD-7^49^		x	x	x	x	
International Trauma Questionnaire (ITQ)^50^		x	x	x	x	
Adult Service Use Schedule (AD-SUS)^51^		x			x	
Beliefs related to diagnosis and intervention		x			x	
Clinical Global Impression—Improvement Scale (CGI-I)^52^ rated by participant					x	
CGI-I rated by participant-nominated person					x	
Measure of satisfaction					x	
Review/reporting of patient AEs/SAEs		x	x	x	x	
Qualitative Interviews						
Informed consent for qualitative interview (select participants)						x
Qualitative interviews with select sample of participants and trial therapists						x

*Participants will be asked at T3 (end of trial period) whether there have been any changes regarding medication, relationship status and employment status and any changes recorded.

EMDR, eye movement desensitisation and reprocessing therapy; FND, functional neurological disorder; NPC, neuropsychiatric care; RA, research assistant.

### Recruitment and timeline for participants

#### Recruitment

Potential participants will initially be screened as part of routine neuropsychiatric appointments. The psychiatrist will verbally introduce the trial to potentially eligible participants and ask for permission for the RA to contact them. Potentially eligible participants’ names will be passed to the CI, who will check that they likely meet the eligibility criteria. The RA will provide potential participants with a summary of the study and will send the Participant Information Sheet and informed consent form for them to review (see online supplemental material). They will have the opportunity to ask any questions they may have. If willing to participate, the RA will obtain informed consent and arrange a screening interview.

The screening interview will be used to establish eligibility in terms of inclusion criterion “Reporting at least one traumatic event on the International Trauma Exposure Measure (ITEM)”, and exclusion criterion “Diagnosis of dissociative identity disorder or score in clinical range on ‘identity disturbance’ subscale of Multiscale Dissociation inventory (MDI)”.^37 38^ The (ITEM) will be used to assess previous adverse experiences. If they meet this inclusion criterion, potential participants will then complete the MDI, which will screen for clinical levels of dissociative ‘identity disturbance’. Potential participants need to score in the non-clinical range of the subscale ‘Identity Disturbance’ on the MDI to take part (score <15). Eligible participants will complete additional baseline measures, as well as completing demographic information, medical history and listing any previous psychological therapies attended for any difficulty (not just FND).

The flow of participants is illustrated in figure 1.

**Figure 1 F1:**
[figure not shown]
Consolidated Standards of Reporting Trials flow diagram for MODIFI study. NPC, neuropsychiatric care.

### Incentives

Participants will be reimbursed for research-related travel costs, up to the value of £20 per appointment (for those who choose to attend appointments in-person, rather than virtually). A non-contingent £25 incentive will be offered to participants for taking part 9 months after informed consent, unrelated to whether they complete the trial or not.

### Allocation and blinding

Consenting participants will be randomised into EMDR (plus NPC) or NPC in a 1:1 ratio. A stratified block randomisation (using randomly permuted blocks of sizes 2 and 4) will be used to ensure similar numbers of patients with and without PTSD symptoms (ie, meeting or not meeting PTSD diagnostic criteria as determined by diagnostic algorithm of the International Trauma Questionnaire (ITQ)) are (relatively) equal across arms. Randomisations will be carried out by the trial manager using the randomisation function on REDCap.

### Blinding

The trial is a single-blind trial with the RA and statistician remaining blind to treatment allocation. It is not possible to blind participants or treating clinicians to randomisation outcome.

### Analysis and statistical methods

#### Sample size

This is a feasibility trial; as such, a power calculation is neither possible nor necessary. Rather, the sample size is pragmatic. Target recruitment is 50 patients in total (25 in each arm), which is consistent with those recommended for pilot and feasibility studies to provide sufficiently reliable estimates of feasibility outcomes, for example, recruitment, adherence and attrition rates and adequate precision of means and variances to inform a fully powered RCT.^39–41^

#### Statistical analysis plan

Data analysis will follow a statistical analysis plan, formally agreed with the trial steering committee prior to analysis, and centred on describing key process measures to decide if a definitive trial is feasible. Participant throughput will be summarised in an extended CONSORT diagram (Eldridge *et al* 2016).^42^

Feasibility outcomes will be summarised using descriptive statistics, with 95% CIs provided to permit assumptions when planning the main trial. Data relating to (serious) adverse events, assessment, screening and recruitment logs will be used to produce accurate estimates of safety, eligibility, recruitment and consent rates in the study population. To determine the adequacy of study inclusion and exclusion criteria, and the generalisability of the trial to the FND population, baseline sociodemographic and clinical characteristics will be compared between study participants and ineligible and non-consenting patients. Intervention adherence (eg, EMDR session attendance) and satisfaction of care data will be used to contribute to the evaluation of the acceptability of allocated intervention/treatment arms and mean EMDR fidelity scores for rated sessions calculated to assess intervention fidelity. At each time point, retention rates will be estimated for each of the patient reported/clinical outcome measures, with consideration given to differential dropout between the arms of the trial, to identify potential (attrition) bias in treatment completion and/or data collection. EMA completion rates in each 2-week assessment period will be calculated with respect to daily assessment. All feasibility outcomes will be compared with relevant full-trial progression criteria.

Baseline characteristics will be reported according to treatment arm. Continuous variables will be reported as mean (SD) if normally distributed or median (interquartile range) if non-normal, while categorical variables will be presented as frequency (%). Subsequent analyses will summarise the proposed patient-reported and clinical outcomes (eg, quality of life and depression measures, (2-week mean) EMA symptom ratings) at each time point for each trial arm using appropriate descriptive statistics (eg, group mean, SD). To provide an indication of potential changes in scores/frequencies between the four time points, linear/logistic mixed-effects regression models will be employed performed on an intention-to-treat basis (accounting for data assumed to be missing at random). These random intercept (mixed) models will include intervention group, time and intervention group-by-time interaction. There will be no emphasis on hypothesis testing, however, which is reserved for the future main trial. Rather, pre-to-postintervention standardised effect sizes (Hedges’ g, relative risk) will be computed (SDs will be computed from estimated model standard errors) with associated CIs calculated to explore imprecision around effect sizes (Durlak 2009).^43^ Due to the small sample size, important covariates (eg, baseline score on relevant measure, gender, age) may be included in models if the two arms happen to be highly imbalanced. Additional analyses (using mixed effect models) focused on ‘per-protocol’ outcomes and the potential value of the (intensively) collected EMA data on FND symptoms will also be administered (see online supplemental material for additional detail).

A descriptive assessment of healthcare utilisation stratified by treatment arm will also be presented. The Adult Service Use Schedule (AD-SUS) will be used to record previous 6 months of health and social care resource use at baseline (T0) and 9 months of health and social care resource use at 9 months (T3). The acceptability of the AD-SUS will be assessed and key items of resource use for a future RCT will be identified. EQ-5D-5L utility scores will also be calculated. A cost-effectiveness analysis will not be conducted.

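### Baseline adjustment depends on observed arm imbalance with no threshold, so the model can differ between outcomes and gives up some precision; one pre-specified model should replace it

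*Protocol article*

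**What the plan says.** All references are to the protocol article.

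- **Model terms.** Under Statistical analysis plan, the random-intercept models "will include intervention group, time and intervention group-by-time interaction". They cover four time points, which Study design defines as T0, T1, T2 and T3, so the baseline score is itself a response.
- **Covariates.** The same section says that "important covariates (eg, baseline score on relevant measure, gender, age) may be included in models if the two arms happen to be highly imbalanced". The list is given as examples, inclusion is optional, and no degree of imbalance is named.
- **Randomisation.** Under Allocation and blinding, "A stratified block randomisation (using randomly permuted blocks of sizes 2 and 4) will be used", with the aim of "similar numbers of patients with and without PTSD symptoms". The factor is whether the ITQ diagnostic algorithm is met. It appears neither among the model terms nor among the example covariates.
- **Use of the results.** Study objectives says that the outcome showing the largest effect will be identified and used to size the substantive trial, and Primary objectives and outcome measures repeats this purpose. The effect sizes are pre-to-post Hedges' g or relative risk, with intervals. Formal testing is left to the main trial.

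**The concern.** A covariate rule triggered by observed imbalance makes the model a function of the data. The baseline score is a different variable for each outcome, so the rule could fire for one questionnaire and not for another. Their effect sizes would then come from different models just when they are being ranked. With no threshold, two analysts could apply the rule differently to the same data.

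There is also a cost in precision. Adjusting for baseline is useful whether or not the arms look balanced, because it removes outcome variance that the baseline score predicts. Reserving it for imbalance gives up part of that gain in a trial of 25 per arm whose main quantitative product is estimates and intervals.

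**Working it through.** **Inputs.** There are 50 patients, 25 per arm, allocated 1:1 (Sample size; Allocation and blinding). The plan has no power figure to reproduce, since Sample size says "a power calculation is neither possible nor necessary"; 2 × 25 = 50 is the only arithmetic. The correlation rho between baseline and follow-up is not given and is assumed to lie between 0.3 and 0.9. I take time as categorical, equal SDs at each visit, complete data, and the between-arm difference in change as the contrast of interest.

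**Step 1: precision.** In SD units, with n = 25 per arm:

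- Stated model (group-by-time contrast, T0 a response): variance = (2/n) × 2(1 − rho).
- Pre-specified baseline adjustment: variance = (2/n) × (1 − rho²).
- Ratio, stated to adjusted: 2/(1 + rho). The interval-width ratio is its square root.

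At rho = 0.5 the half-widths are 1.96 × √(0.08 × 1.0) = 0.554 and 1.96 × √(0.08 × 0.75) = 0.480.

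| rho | half-width, stated | half-width, adjusted | variance ratio | stated CI wider by |
|---|---|---|---|---|
| 0.3 | 0.656 | 0.529 | 1.54 | 24.0% |
| 0.5 | 0.554 | 0.480 | 1.33 | 15.5% |
| 0.7 | 0.429 | 0.396 | 1.18 | 8.5% |
| 0.9 | 0.248 | 0.242 | 1.05 | 2.6% |

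**Step 2: how often the trigger could fire.** By chance alone, a standardised baseline difference has standard error √(2/25) = 0.283. It exceeds 0.25 with probability 37.7% and 0.5 with probability 7.7%. For at least one of three independent continuous covariates the figures are 1 − (1 − 0.377)³ = 75.8% and 1 − (1 − 0.077)³ = 21.4%. Both cut-offs are assumed, because the plan has none.

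**Step 3: what switching does to an estimate.** Let d be the baseline difference and b the slope of follow-up on baseline (equal to rho when SDs are equal). The change estimate minus the adjusted estimate is then −(1 − b)d. For d = 0.5 SD the shift is 0.25 SD at rho 0.5 (0.5 × 0.5) and 0.05 SD at rho 0.9 (0.1 × 0.5).

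**Step 4: model fits.** Mixed models were fitted to 60 simulated complete-data trials (25 per arm, four time points, within-stratum correlation 0.6, assumed PTSD shift 0.6). Mean standard errors of the 6-month contrast were:

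- stated model: 0.2528
- stated model plus PTSD main effect: 0.2528, estimate unchanged
- stated model plus baseline score, T0 still a response: 0.2528, estimate unchanged
- T1–T3 as responses with baseline score: 0.2286; with PTSD added, 0.2269
- T0 means constrained equal: 0.2282; with PTSD added, 0.2260

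If the trigger fired and T0 stayed a response, adding the baseline score would therefore not sharpen the group-by-time contrast. The gain comes only from moving T0 out of the responses or constraining its means.

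**Step 5: error rate under the rule.** In 40,000 simulated trials per correlation, switching from change score to baseline adjustment at the two assumed cut-offs gave a nominal 5% error of 3.7–4.1% at rho 0.5 and 4.1–4.4% at rho 0.7.

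**The case against.** The strongest defence has four parts.

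1. **The baseline is already in the model.** This is correct. A reader might infer that baseline information is discarded, but T0 is a response, so the loss is only that between a change score and an adjusted analysis. A reader might also headline that adjustment is worth 50/0.75 ≈ 67 patients instead of 50. That figure belongs to rho 0.5 alone; at rho 0.9 it is 50/0.95 ≈ 53.

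2. **Omitting the stratum does no measurable harm here.** This largely stands. A reader might infer that leaving PTSD status out makes the standard error wrong. For the linear group-by-time contrast with complete data, neither the estimate nor the standard error changes. Nor do the documents support an argument through attrition: nothing in them links PTSD status to dropout.

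3. **A separate plan will be agreed with the steering committee before analysis, and the statistician is blind to allocation.** That plan could set a threshold or add the stratum, and blinding limits deliberate choice. Neither removes the difficulty, because the article itself commits to adjustment conditional on imbalance, and a threshold would still let the model differ by outcome.

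4. **This is a feasibility trial.** The progression criteria in Table 3 use screening attendance, therapy completion and outcome completion, none of them a modelled effect. That limits the importance of the point, but the effect sizes still feed outcome choice and the next sample size.

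A reader might also infer that T0 would be regressed on itself and distort the effect size. The article does not say that T0 would remain a response once baseline was a covariate, nor which standard errors would be converted to SDs, so this cannot be asserted.

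**Conclusion.** The point holds in a limited form. The plan states a data-driven covariate rule with no threshold, and it allows different models for outcomes that are to be compared with one another. The precision given up is moderate at low correlation and slight at high correlation: intervals about 24% wider than needed at rho 0.3, falling to 2.6% at 0.9. It is not a validity failure. The simulated error rates under the rule are somewhat conservative, and no progression decision depends on it. The change is worth making because it costs almost nothing.

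The figures rest on an assumed rho, assumed imbalance cut-offs, an assumed PTSD shift, categorical time and complete data. They do not carry over to the logistic models.

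**What to change.** Delete the imbalance trigger. For every continuous outcome with a baseline value, name one model in advance:

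- **Preferred:** T0–T3 as responses, with T0 means constrained equal across arms and a group effect at each of T1, T2 and T3. This keeps patients who have no follow-up.
- **Alternative:** T1–T3 as responses, with baseline score as a covariate plus group, visit and group-by-visit. This drops patients with no follow-up.

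In either form, add PTSD status at randomisation as a main effect, to match the stratified design rather than for any large gain. Fix any further covariates, such as age or gender, in advance for all outcomes or leave them out. Both options require the baseline value to be recorded before allocation is known, which the plan should state. For the MDI, which Table 4 schedules at screening rather than T0, the screening score would take that role.

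The cost is wording. With categorical time the stated model has 8 fixed effects (1 + 3 + 1 + 3). The preferred model with PTSD also has 8 (1 + 3 + 3 + 1), as does the alternative with a common baseline slope (1 + 2 + 1 + 2 + 1 + 1). Letting the baseline slope vary by visit would add 2. No new data are needed: ITQ status is required for randomisation, and the baseline scores are already scheduled.
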